Examination of the effects of the InCoPE-App on physical and cognitive performance in people with dementia will be determined based on the listed variables in Table 1. The primary outcomes will be assessed before and after the 18-week intervention. To assess quality of life, the 13-item caregiver-administered version of Quality of Life-Alzheimer’s Disease (QOL-AD) [27] will be applied. The QOL-AD is a valid and reliable tool (internal reliability, α=0.88-0.89; test-retest reliability for caregivers, 0.92) [27]. Global cognition will be assessed with the MMSE [28]. The questionnaire will be implemented in the InCoPE-App. The MMSE easily assesses 7 areas of cognitive function, with sufficient test-retest reliability (0.80-0.95) [28,36]. To assess executive function, the Digit Span Test [29] will be administered. The Digit Span Test consists of 2 parts: forward and backward. Participants will be asked to repeat a sequence of 3 to 9 digits forward and of 2 to 8 digits backward. The InCoPE-App will be used to document the given answers. The Digit Span is a reliable and valid test [37].

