### Sample Size

The sample size for the number of nursing assistants who will evaluate the InCoPE-App with regard to usability was defined using a probabilistic model of problem discovery for formative user research [34]. We defined a sample size comprising 22 participants to have a 90% chance of observing with a probability of 0.1. In the second study phase, outcomes also include usability in addition to the effectiveness of the InCoPE-App with respect to adaptations in physical and cognitive performance in people with dementia. For this reason, each participant will recruit 2 appropriate residents with dementia in accordance with our inclusion and exclusion criteria. We anticipate that our calculated sample size (N=44: intervention group [IG], n=22; control group [CG], n=22) will be appropriate to examine potential trends toward effectiveness of the InCoPE-App.

This sample size allows detection of moderate effects calculated using an ANOVA with repeated measures for within and between interactions. The calculation of the sample size with G*Power version 3.1.9.2 (Heinrich Heine University of Dusseldorf, Germany [47]; effect size ηp² = 0.07, α error probability .05, power 0.95) resulted in 44 participants.

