### Statistical Methods

All analyses will be performed using SPSS 27.0 (IBM Corp, Armonk, NY). Prior to analysis, plausibility (eg, considering range and distribution) will be checked to minimize errors. The quantitative analysis comprises the evaluation of the usability questionnaires, which will be analyzed with respect to the corresponding guidelines and will be compared with representative data.

The baseline values of physical and cognitive performance will be compared between IG and CG using chi-square tests for categorical data, Mann-Whitney *U* tests for nonparametric variables, and t tests for continuous and normally distributed parameters. Normal distribution will be checked with the Shapiro-Wilk test. Means and standard deviations will be calculated for normally distributed data, and medians and interpercentile ranges will be calculated for non-normally distributed data. A 2-factor ANOVA with repeated measurement will be used to identify treatment effects. In addition, 95% confidence intervals and partial Eta² will be calculated. The log events will be summarized and analyzed descriptively. Potential effects among subgroups based on varying physical or cognitive performance, gender, fear of falling, and logged events (completed training sessions, average duration of the training sessions) will be investigated using chi-square tests and *t* tests.

Qualitative content analysis of the field notes will be conducted [48]. The interviews will be fully transcribed and checked for accuracy. The entire coding process will be independently performed by 2 scientists. The transcripts will be reviewed to identify meaningful content-related aspects. These aspects will be systematically described using a category system. Research questions and interview guidelines will be consulted to deductively derive the main categories. Subcategories will be inductively developed based on the findings (eg, by subsumption). The category system will be tested by 2 scientists who will independently test-code several parts of the qualitative material and subsequently adapt the categories and their definitions. The 2 coding systems will eventually be merged by consensual coding where consensus will be reached.

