### Strength and Limitations

Through the innovative and timely development method and thorough evaluation and integration of users’ experiences [49], we expect an application that is highly usable and feasible in everyday care situations. The acceptance of the InCoPE-App will promote its regular usage and thus allow testing and training residents with dementia individually. The regular conduct of physical and cognitive tests that is implemented as an essential part of the app will help to document the progression of disease symptoms and can thus be regarded as an additional objective tool for clinical documentation, which is required on a regular basis in a nursing home setting. The individualization of the exercise program, which has been described as critically important in previous research [9,20], is the key innovative and novel component of the InCoPE-App.

It is unlikely but possible that usability of the InCoPE-App will be rated as low by nursing assistants. In this case, fundamental changes within the application will be required to increase acceptance and practicability, which may have a considerable impact on the effectiveness of the exercise program. There are risks from a technical point of view that might impede the usability of the InCoPE-App, such as possible failure of the tablets to store the data on each tablet. To lower this risk, we will provide the required tablet with the installed InCoPE-App for each participating nursing home. In addition, nursing assistants can contact the research team to report technical issues and get help at any time.

Another limitation is the rather small number of participating people with dementia. This sample size is sufficient to detect moderate within and between interactions. However, it might be too small to statistically detect small effects. The use of the InCoPE-App within everyday life allows us to gain information about everyday feasibility and suitability; thus, results can be more easily transferred to daily routine. 

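### The 95% power claimed at partial eta squared 0.07 with N=44 holds only on a different effect-size scale; on the scale the planned ANOVA reports, power is about 0.42

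*Protocol article*

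**What the plan says.** The Sample Size section of the protocol article gives the planning inputs and the result together: "effect size ηp² = 0.07, α error probability .05, power 0.95) resulted in 44 participants". The test is the within-between interaction of a repeated-measures ANOVA in G*Power 3.1.9.2, and the allocation is "N=44: intervention group [IG], n=22; control group [CG], n=22". The section concludes: "This sample size allows detection of moderate effects calculated using an ANOVA with repeated measures for within and between interactions". The Strength and Limitations section repeats this: "This sample size is sufficient to detect moderate within and between interactions".

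On measurement and analysis, the Primary Outcomes section says "The primary outcomes will be assessed before and after the 18-week intervention". The Statistical Methods section says "A 2-factor ANOVA with repeated measurement will be used to identify treatment effects" and adds "In addition, 95% confidence intervals and partial Eta² will be calculated". The software is SPSS 27.0.

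The article gives neither the effect-size option chosen in G*Power nor the pre-post correlation.

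**The concern.** Planning and reporting carry the same label, partial eta squared, so a reader will set the 0.07 in the sample size paragraph beside the partial eta squared in the results table. The two are on the same scale only if the planning value was entered on the scale that SPSS reports. With 22 residents per group, 95% power at 0.07 on that scale is not plausible: with two groups and two occasions the interaction test is a two-sample t test on change scores, and 0.07 corresponds to about 0.55 SD of change.

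At stake is the stated sensitivity of the effectiveness part of the trial. If the claim is on the wrong scale, the design would miss an effect of the stated size more often than it detected it, while two sections of the article say that the sample is sufficient.

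**Working it through.** **Inputs from the protocol article.** Two groups of 22, N=44 (Sample Size). Two occasions, m=2 (Primary Outcomes). Interaction test with df 1 and N−2=42. Partial eta squared 0.07, alpha .05, power 0.95 (Sample Size). **Assumed, because not stated:** the G*Power default effect-size option and ρ=0.5. These enter step 1 and the account of it in step 4, but not steps 2 and 3.

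**Step 1: reproduce the plan's 44.**
- f² = 0.07/(1−0.07) = 0.0753, so f = 0.274.
- In the default G*Power convention the noncentrality is λ = f²·N·m/(1−ρ). At m=2 and ρ=0.5 the multiplier is 2/0.5 = 4.
- λ = 0.0753·44·4 = 13.25, and power at df 1, 42 is 0.945.
- With f entered as 0.28, partial eta squared is 0.28²/(1+0.28²) = 0.0727, which rounds to 0.07. Power is then 0.952 at N=44 and 0.943 at N=42, so the answer is exactly 44.
- The stated 44 therefore reproduces in this convention. Its power at N=44 (f=0.274) varies with ρ: 0.71 at 0, 0.85 at 0.3, 0.945 at 0.5, 0.996 at 0.7.

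**Step 2: the same 0.07 on the scale the analysis reports.** In a 2×2 mixed design the interaction F is the square of the two-sample t on change scores, and partial eta squared = F/(F+42). No ρ enters.
- λ = f²·(N−2) = 0.0753·42 = 3.16 gives power 0.412.
- λ = f²·N = 0.0753·44 = 3.31 gives power 0.428. A simulation of 200,000 trials gave 0.427.
- If 0.07 is a rounded value (0.065 to 0.0749), power is between 0.39 and 0.45.
- First even N with power of at least 0.95: 176 (λ=f²·N) or 178 (λ=f²·(N−2)). For 0.80: 108 or 110.

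**Step 3: an observed value of 0.07.** F = 42·0.07/0.93 = 3.16 and p = 0.083. The 5% critical value is F(1,42) = 4.07, so the smallest significant observed value is 4.07/(4.07+42) = 0.088. An observed effect equal to the planning value would not be significant.

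**Step 4: what N=44 does detect on the reported scale.**

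| Power | λ needed (df 1, 42) | Partial eta squared, λ/(λ+44) to λ/(λ+42) | Difference in change, 2·√(λ/44), in SDs of the change score |
|---|---|---|---|
| 0.80 | 8.22 | 0.157 to 0.164, about 0.16 | 0.86 |
| 0.95 | 13.62 | 0.236 to 0.245, about 0.24 | 1.11 |

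The λ of 13.25 from step 1 corresponds to 0.23 to 0.24 on this scale. The factor of 4 in λ accounts for the gap between 0.07 and about 0.24.

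All figures treat residents as independent and assume no dropout.

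**The case against.** The best defence is that nothing was miscalculated. The named software returns 44 under its default option with ρ=0.5 and f=0.28. This stands. A reader might infer an arithmetic error, or that the answer should have been 46 because f=0.274 gives 0.945 at 44. That gap is no more than the rounding of 0.07.

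It can also be said that the convention and ρ are inferred, and that a condensed article may leave such settings to the full protocol. That stands too, so their absence is not the point. The result on the reported scale needs neither.

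A third argument is that moderate is not refuted on every scale. A reader might infer that N=44 detects only a large effect of 1.1 raw SDs. That holds only at ρ=0.5, where the SD of change equals the raw SD. In general the raw-SD value is the change-SD value times √(2(1−ρ)), so the difference detectable with 95% power is 0.86 raw SD at ρ=0.7, 0.70 at 0.8 and 0.50 at 0.9. The article quotes test-retest reliabilities of 0.92 for QOL-AD, 0.80 to 0.95 for MMSE and 0.72 to 0.99 across the physical tests. The 18-week correlation is not given and is probably lower. This limits what can be said in raw units, but it does not rescue 0.95 at a partial eta squared of 0.07 as the analysis will report it.

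Finally, the aim is softened. The article speaks of trends toward effectiveness, lists the small sample as a limitation, and also derives its numbers from a usability model for 22 nursing assistants. That lowers the consequence but does not withdraw the power statement.

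**Conclusion.** The point holds in a limited form. The article states power 0.95 for partial eta squared 0.07 at N=44. On the scale that its own planned ANOVA reports, power is 0.41 to 0.43, and 0.95 would take about 176 to 178 residents, four times the plan. These figures rest only on two groups of 22, two occasions, a 5% F test and independent residents. That the 44 came from the default G*Power convention at ρ of about 0.5 is an inference from the result.

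Two further readings are not supported. A reader might infer that the limitations text says only small effects could be missed. It says that the sample might be too small for small effects and that it suffices for moderate interactions; the second statement is the one at fault. A reader might also infer that a null result will be taken as evidence against a moderate benefit. No section says so; that is a risk from the wording, not a planned conclusion.

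The trial is cluster-randomized, and the stated calculation shows no allowance for it. Positive correlation within homes, or dropout, would lower the power figures, so they are upper limits.

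**What to change.** Keep N=44, the design and the analysis. In the Sample Size section, and in matching form in Strength and Limitations, replace the unqualified claim of 95% power for moderate effects with:

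> On the partial eta squared scale reported by the planned ANOVA, N=44 gives 80% power for about 0.16 and 95% power for about 0.24 (between-group difference in change of about 0.86 and 1.11 SDs of the change score); power for 0.07 is about 0.42. These power figures are upper limits, before allowance for cluster randomization and dropout.

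If the authors also want to express the detectable effect in raw SD units, they must state the pre-post correlation assumed for the conversion. No request for confidence intervals is needed, because the Statistical Methods section already plans them.

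The cost is wording only. No residents are added, and the stated power becomes less favourable.

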## Introduction

The COVID-19 pandemic has had drastic consequences for all areas of everyday life. In many nursing homes, routine processes had to be changed. Some activities and treatments were reduced or, in areas, canceled. Hygiene and safety measures (eg, no external exercise instructors, no group settings) and the increased workload for nursing assistants led to suspending physical exercise programs and activities, especially when delivered in a group setting. The potential consequences for nursing home residents include reduced general activity accompanied by decrease in cognitive function and physical performance and a considerable loss of an individual’s quality of life. Furthermore, these COVID-19–induced changes may also have an economic impact and may increase care expenses in the long term.

Dementia is present in up to 50% of nursing home residents [1]. The clinical symptoms of this neurodegenerative disease include, but are not restricted to, decreased cognitive skills and reduced physical performance (eg, balance and mobility) [2,3]. Many people with dementia experience a rapid progression of the disease [1]. Thus, people with dementia might be seriously affected by COVID-19–induced reduction of physical or mentally stimulating activities and similar treatments (eg, physiotherapy, ergo therapy, social interactions) in nursing homes.

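### The planned enrolment of 44 residents equals the number the power calculation needs analysed, so the stated power of 0.95 carries no allowance for loss over 18 weeks

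*Protocol article*

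**What the plan says.** In the protocol article, Sample Size describes a calculation for an "ANOVA with repeated measures for within and between interactions", with "effect size ηp² = 0.07, α error probability .05, power 0.95) resulted in 44 participants". The same section then fixes the enrolment: "We anticipate that our calculated sample size (N=44: intervention group [IG], n=22; control group [CG], n=22) will be appropriate" for looking at trends towards effectiveness. The figure of 44 comes from 22 nursing assistants with two residents each, and the abstract repeats it.

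Other sections bear on the point:

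- **Study Design** sets two residents per nursing assistant as a minimum. Primary Outcomes and Sample Size give two as the number.
- **Primary Outcomes** schedules the effectiveness measures before and after the 18-week programme.
- **Statistical Methods** names a two-factor repeated-measures ANOVA for the treatment effect.
- **Participants** admits residents older than 65 with an MMSE of 10 to 24, and the Introduction remarks: "Many people with dementia experience a rapid progression of the disease".
- **Strength and Limitations** concedes that small effects may be missed, but states: "This sample size is sufficient to detect moderate within and between interactions". Attrition is not mentioned there.

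**The concern.** With one value before and one after, the group-by-time interaction is a comparison of change scores. A resident without the second value has no change score and drops out of the test that was powered. The number from the calculation is therefore a number of complete pairs, while the planned number is a number of residents enrolled. The two are equal, so the claimed power leaves no room for a death, a withdrawal or a missed final assessment.

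At stake is how the result will be read. If the trial shows no significant interaction, a reader who takes 0.95 at face value will assume a 5% chance of having missed the assumed effect. With some residents lost, that chance is larger, and nothing in the article says so. The equality of the two numbers is visible on the page, so this is not a matter of detail that a condensed article leaves to a fuller document.

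**Working it through.** **Inputs from Sample Size:** partial eta squared 0.07; "α error probability .05"; power 0.95; allocation "N=44: intervention group [IG], n=22; control group [CG], n=22". Primary Outcomes gives two measurements.

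**Inputs not in the document (assumed):** pre-post correlation ρ = 0.5, the G*Power default; loss rates of 10% to 30%.

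**Formulas**

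- f² = ηp²/(1 − ηp²)
- noncentrality λ = N × f² × m/(1 − ρ), with m = 2 measurements
- power = probability that a noncentral F with 1 and N − 2 degrees of freedom and noncentrality λ exceeds the central 5% critical value

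**Step 1: reproduce the plan's figure.** f² = 0.07/0.93 = 0.0753, so f = 0.274. At N = 44, λ = 44 × 0.0753 × 2/0.5 = 13.25, the critical value of F(1, 42) is 4.07, and power is 0.945. The smallest N that reaches 0.95 is 46. With f rounded to 0.28, power at 44 is 0.952 and 44 is exactly the minimum. Either way, 44 is the number that must be analysed, with nothing in reserve.

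**Step 2: power when pairs are lost** (ρ = 0.5)

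| Complete pairs | Lost of 44 | λ | Power, f = 0.274 | Power, f = 0.28 |
|---|---|---|---|---|
| 44 | 0 | 13.25 | 0.945 | 0.952 |
| 40 | 4 (9%) | 12.04 | 0.922 | 0.932 |
| 35 | 9 (20%) | 10.54 | 0.883 | 0.895 |
| 31 | 13 (30%) | 9.33 | 0.840 | 0.854 |

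The λ column is for f = 0.274. On that column the chance of missing the assumed effect rises from about 5.5% to 11.7% at 20% loss and 16.0% at 30% loss. With f = 0.28, one loss already takes power below 0.95 (0.948 at 43 pairs). Power stays at 0.80 or above down to 29 pairs (0.813), a loss of 15/44 = 34%.

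**Step 3: dependence on the unstated correlation** (f = 0.274)

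| ρ | 44 pairs | 40 | 35 | 31 |
|---|---|---|---|---|
| 0.3 | 0.852 | 0.815 | 0.759 | 0.704 |
| 0.5 | 0.945 | 0.922 | 0.883 | 0.840 |
| 0.6 | 0.978 | 0.966 | 0.941 | 0.910 |
| 0.7 | 0.996 | 0.992 | 0.982 | 0.968 |

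Of these four values, only ρ = 0.5 returns about 44 residents for power 0.95. The others give 63 at 0.3, 37 at 0.6 and 28 at 0.7.

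**Step 4: for orientation, enrolment that would keep 44 pairs.** N = 44/(1 − loss), rounded up: 49 at 10%, 55 at 20%, 63 at 30%.

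All figures treat residents as independent. The trial is cluster randomized, which is a separate matter.

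**The case against.** Several points on the other side have weight.

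- **No attrition figure exists in the document.** A reader might infer that the trial is bound to end with fewer than 44 complete pairs. The article does not support that: it gives no loss rate, and a resident in hospital or quarantine is lost only if the final assessment is missed altogether, not if it is delayed. Participants also contains some protection: general practitioner clearance, exclusion of severe acute disease and severe motor impairment, and at least 18 weeks' employment for nursing assistants. What stands is narrower: the stated power has no reserve if losses occur.
- **The claim depends on ρ.** A reader might also infer that 0.95 fails with the first lost resident whatever the data look like. That holds only on the convention behind the 44. At ρ = 0.6, 40 pairs still give 0.966. The test-retest values quoted under Primary Outcomes run from 0.72 to 0.99 for the QOL-AD, the MMSE and the physical tests. They are not 18-week correlations, but they show that 0.5 is not the only candidate. A lower ρ cuts the other way. This objection stands, and it is why the assumed correlation has to be stated.
- **The recruitment wording in Study Design permits more than two residents per assistant.** It allows over-recruitment but plans none, because no target above 44 appears anywhere. It leaves a wording conflict to settle.
- **The effect is small beside the stated aim.** Power of 0.84 to 0.92 is still respectable, the aim is partly described as trends, and the sufficiency sentence in Strength and Limitations names no power level. This limits the weight of the point, but Sample Size still puts 0.95 on the page.
- **Final assessments are already scheduled for everyone.** That is so, but the article does not say that they go ahead after training has stopped.

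**Conclusion.** The point holds as a modest overstatement of power. Enrolment equals the uninflated result of the calculation, and the planned analysis uses complete pairs only, so the figure of 0.95 applies only to 44 residents with both assessments. At an assumed 10% to 30% loss, power on the sponsor's apparent convention is about 0.92 to 0.84. This rests on ρ = 0.5, on assumed loss rates and on independent residents.

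The documents do not support saying that the trial is badly underpowered on this ground, or that losses are certain. What needs changing is the unconditional wording in Sample Size and in Strength and Limitations.

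**What to change.** Keep N=44 and make five changes to the wording.

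1. **Sample Size:** say that power 0.95 refers to 44 residents with both assessments, and give the pre-post correlation that was assumed.
2. **Sample Size:** add that, if 10% to 30% of residents lack the final assessment, power is about 0.92 to 0.84 (if the correlation was 0.5), before any correction for clustering. Label the loss rates as assumptions.
3. **Strength and Limitations:** qualify the sufficiency sentence in the same terms.
4. **Study Design, Primary Outcomes and Sample Size:** reconcile the minimum of two residents per nursing assistant with the fixed number of two, so that it is clear whether 44 is a target or a floor.
5. **Primary Outcomes:** state that the scheduled post-assessment is carried out for every enrolled resident who is alive and consenting, whether or not training continued. This concerns data collection only.

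The cost is protocol wording and a slightly less favourable stated power. No extra residents or instruments are needed, since the post-assessment is already planned. These changes do not restore power; they make the stated figure accurate and limit avoidable loss of pairs.
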